## Abstract

**Background:**

Chemotherapy-induced side effects may have a negative effect on nutrition intake, thus increasing the risk of malnutrition and consequently, other serious complications for patients with cancer. The prevalence of malnutrition is common among patients with colorectal cancer. Nurse-led empowering education may have a positive effect on self-care activity in this patient group. Therefore, our purpose is to develop an empowering educational nursing intervention and test its effect on self-care activation and knowledge level among patients with colorectal cancer during chemotherapy. Secondary outcomes are quality of life and risk of malnutrition.

**Methods:**

An interdisciplinary expert group developed a face-to-face empowering educational intervention using teach-back method. A two-arm, single-centre, superiority trial with stratified randomisation (1:1) and pre-post measures will be used to assess the effect of the intervention compared to standard care. Patients (*N* = 40 + 40) will be recruited in one university hospital outpatient clinic in Finland. Eligibility criteria are adult patients diagnosed with colorectal cancer starting oral fluoropyrimidine or combination chemotherapy treatment. A registered nurse experienced in oncology will deliver the intervention 2 weeks after the first chemotherapy. Outcomes are measured before intervention (M0) and after a two-month follow-up period (M1).

**Discussion:**

This study will assess whether nurse-led empowering education using teach-back method is effective on self-care activity among patients with colorectal cancer. If the intervention has a positive effect, it may be implemented into patient education in a corresponding context.

**Trial registration:**

ClinicalTrials.gov: NCT04160650 Registered 12 November 2019 - retrospectively registered

## Background

People are increasingly affected with colorectal cancer (CRC), which is one of the most prevalent cancers globally, comprising about 10% of newly found cases [1, 2]. In Finland, about 3300 patients are diagnosed annually with CRC, making it the second common cancer type among both men and women [3]. Chemotherapy is a common treatment for patients with operated high-risk stage II and III CRC as well as advanced and metastatic CRC [4]. Chemotherapy-related toxicities that affect the ability to eat are known as nutrition impact side effects (NIS). Side effects such as nausea, diarrhoea, constipation, mouth sores, heartburn, loss of appetite, altered taste, cold sensitivity, pain, fatigue and distress may lead to inadequate nutritional intake and weight loss, thus increasing the risk of malnutrition [5–8].

Malnutrition is common among patients with CRC, the prevalence varying according to patients’ age, cancer type and stage of cancer [7, 8]. In malnutrition, a deficiency or excess of energy, protein, and other nutrients causes measurable adverse effects on body function and clinical outcome [9]. The prevalence of both malnutrition and NIS are higher in older population [10]. For example, among geriatric patients with gastrointestinal system cancer (*n* = 153) about 38% were malnourished and 35% at risk of malnutrition at the time of the first outpatient visit. Chemotherapy has been shown to increase the incidence of malnutrition and weight loss [7, 11]. The complications of severe malnutrition may lead to greater chemotherapy toxicity, worse physical function and quality of life (QoL), and reduced overall survival [12, 13]. Moreover, malnourished inpatients have longer hospital length of stay and higher treatment costs [8]. Therefore, it is essential to develop effective interventions to support empowerment and promote nutrition intake of patients receiving chemotherapy.

Nutrition-related interventions for patients with cancer have been studied extensively with mixed results. Interventions have included individualised nutritional support and counselling to reach protein and energy goals [14], personalised nutrition intervention [15–17], dietary counselling or advice [18, 19], oral nutritional supplements (ONS), and nutrition advice with written information [18]. Interventions have proved to be effective on energy and protein intake [14–19], weight [15], QoL [14, 16, 17, 19], morbidity and mortality [14, 16, 17] as well as the risk of adverse clinical outcomes at 30 days [14]. Among patients with head and neck cancer undergoing radiotherapy, individualised nutritional counselling compared to ad libitum diet and ONS was capable of sustaining a significant impact on patients’ outcomes after 3 months’ follow-up [16]. Conversely, some of the interventions mentioned above have not been effective on weight [18, 19], nutritional status, QoL, functional status [18] and mortality. According to authors, the lack of effect might have been related to small sample sizes, short follow-up periods or low methodological quality of the studies [19]. Alternatively, Internet-based interventions including information and some interactive activities with experts to manage common eating and nutritional problems during cancer treatments have been tested. The results have not shown statistically significant changes on patients’ knowledge levels, anxiety and QoL, probably due to limited sample size or insufficient intervention [20].

Only few studies have explored the effect of nurse-led nutritional interventions among this patient group, yet the results have been promising. A multidisciplinary team approach for nutritional interventions (individual recipes, nutritional risk screening, total energy requirement calculation, education and diet adjustments) conducted by specialist nurses has obtained a positive effect on pre-albumin levels among CRC patients undergoing chemotherapy [21]. An individualised educational program with face-to-face and telephone counselling gained positive results on energy and total protein intake among patients with CRC (*n* = 19 + 21) in palliative care context [22]. The same type of intervention among patients with gastric cancer (*n* = 72 + 72) implemented by a nurse specialist had a positive effect on nutritional intake, haemoglobin, total serum and albumin levels, as well as on chemotherapy compliance rate [23]. Our literature search on the subject did not find other results of nurse-led studies, so there is still a lack of nursing-specific outcomes of nutrition-related interventions. In general, educational nursing interventions have shown positive outcomes on the level of knowledge and symptom severity yet the results have been inconsistent on QoL among patients with cancer [24].

Self-care at home between the chemotherapy cycles has an important role in the success of overall care. Self-care involves both the ability to care for oneself and the activities necessary to achieve, maintain, or promote one’s optimal health. Through self-care, various outcomes may be achieved; for example, improved symptom control, coping with the illness, and QoL. In addition, health services usage and costs may decrease [25]. In this study, self-care is seen as an ability to manage NIS and gain control over one’s health. We use empowering patient education and teach-back method to support patients in their self-care.

Empowerment refers to the ability to manage the challenges of the illness and having a feeling of control over one’s life. It is perceived as an inner strength of a human [26, 27]. Empowerment occurs when individuals’ capacity to think critically and make informed decisions is supported and they make decisions about their own care [28]. Empowerment is created in dialogue in nurse-patient relationship [29] as nurses support patients by offering knowledge and assist them to find, construct and use their own resources in self-care. The dimensions of empowerment can be categorised as experiential (patients’ earlier experiences), functional (function of one’s body and mind), ethical (feeling of being valued and respected), financial (affording support, technical aids), bio physiological (knowing one’s own body and its symptoms), social (interaction with other people) or cognitive (knowledge for improving one’s health) [26, 30]. In this study, empowerment is seen as a process where the nurse supports patients’ empowerment to be more active in self-care. During this process, patients gain knowledge to develop skills for NIS-related problem-solving in daily life [27, 28] in order to reduce the risk of malnutrition and promote the QoL.

Previous studies examining patients’ expectations towards their care demonstrate the expectation of having knowledge [31–33] to manage NIS and own health independently at home. As nutritional care is seen as part of fundamental care [34], nurses have a good opportunity to support patients’ empowerment on self-care of NIS and prevent the risk of malnutrition during chemotherapy. With this research protocol, we answer the question how the empowering educational nursing intervention using teach-back method will be tested on self-care activation, knowledge level (primary outcomes), QoL and risk of malnutrition (secondary outcomes) among patients with CRC during chemotherapy.

## Methods

### Aim, design and setting of the study

The aim of this intervention is to improve patients’ empowerment in self-care. The design is a two-arm, single-centre trial with stratified randomisation (1:1) with repeated measures (Fig. 1). We hypothesise that patients with CRC who receive nurse-led empowering education of NIS vs standard education have higher self-care activation level, better knowledge level, less risk of malnutrition and less worsening of QoL at 2 months’ follow-up compared to the control group (CG).

**Fig. 1 Fig1:**
[figure not shown]
Study design

The study setting is a large university hospital in Southern Finland, responsible for specialised health care for about 2.1 million people. In the Cancer Centre outpatient clinic, about 4500 patients diagnosed with CRC (colon, rectum) receive chemotherapy treatment annually. Up to 40 new patients per month come for an evaluation of chemotherapy initiation.

### Characteristics of participants

Eligible participants are adult men and women diagnosed with CRC, > 18 years and having oral fluoropyrimidine or combination chemotherapy treatment. Exclusion criteria are physical, cognitive or psychological impairment preventing participation and insufficient comprehension of Finnish language.

### Intervention

#### Standard care

Patients both in CG and intervention group (IG) receive standard education delivered by a registered nurse (RN) during the first visit in the outpatient clinic and later on in the infusion unit. Standard education includes the following verbal information:
side effects and their self-care; nausea, diarrhoea, obstipation and sores in the mouth, peripheral neuropathy symptoms, local venous irritation, heart symptoms, mucous and skin irritationself-monitoring of NIS, fluid intake, medication dose changes, effect of chemotherapyweight controltaste alterationcold sensitivityimportance of varied dietoral nutritional supplementsclinical nutritionist services

Standard education includes the following written information:
‘Nutrition guide for cancer patients’‘Instructions for those receiving anticancer treatment’‘Information on strong opioids’‘Cancer pain management’‘Anti-nausea medication’‘When you have nausea’‘Management of diarrhoea’‘Management of constipation’‘Oral care instructions for cancer patients’

In addition to a RN, physicians give patients instructions on medication and related side effects.

#### Intervention protocol

The intervention was developed during autumn 2018 and spring 2019 by an interdisciplinary expert group consisting of two RN experienced in oncology, a clinical nutritionist, an oncologist, and the researcher (LT). We held four shared meetings and additional discussions between each member and the researcher. According to the protocol, patients in IG will receive knowledge of healthy diet and malnutrition. In addition, they will receive tailored knowledge of NIS. The tailoring is based on the side effect self-monitoring diary and patient activation level assessment according to the Patient Activation Measure (PAM) [35]. In addition, patients receive knowledge of the prevention of NIS and self-care strategies based on organisation guidelines. The teach-back method is used to verify participants’ understanding of the received knowledge, to tailor education, to uncover health beliefs, and to activate patients in dialogue [36]. Participants have to be able to teach back the main parts of the knowledge related to malnutrition as well as the reasons, prevalence, and self-care of the NIS they are suffering from. The teach-back method has shown a positive effect in self-care by improving outcomes in disease-specific knowledge, adherence and self-efficacy among people with chronic disease. It has also reduced hospital readmission rates [37].

Empowerment is supported by offering additional knowledge according to patients’ expectations. In addition, the research nurse uses active listening and strengthening self-care strategies that have been successful. The progression of the discourse is based on patients’ expectations and active involvement: the nurse provides the patient with expert knowledge and maintains an empathic connection to the patient throughout the session [38].

The content of the educational intervention is as follows:
Illustrating the purpose of the session.Exploring patients’ current knowledge of healthy diet and malnutrition, offering additional knowledge using teach-back.Bringing forward individual NIS and their intensity on a numerical rating scale (NRS) ≥3, and patients’ knowledge expectations, offering additional knowledge using teach-back.Bringing forward performed self-care strategies and offering additional knowledge using teach-back.Bringing forward individual NIS and their intensity (NRS < 3), offering additional knowledge.Making a brief summary.

Due to the COVID-19 pandemic, the intervention was scheduled for the second chemotherapy course. The intervention will not entail any extra costs for patients. In case the intervention cannot be conducted face-to-face, it is possible to make it available online, e.g. as a video call.

#### Intervention nurse

The eligibility criteria for the research nurse comprise being a registered nurse and experienced in oncology nursing. The research nurse is trained to deliver the intervention by the researcher during three-hour face-to-face sessions held three times. The research nurse answers open-ended questions related to the content and method of education before the intervention commences. The intervention is delivered systematically according to the prescheduled protocol. After each session, the research nurse documents the length and content of the intervention. The researcher and research nurse will meet once a week to check that the protocol is adhered to.

### Outcome measures

Primary outcomes are activation in self-care and knowledge level. Secondary outcomes are risk of malnutrition and QoL. The schedule of enrolment, interventions, and assessments [39] is presented in Fig. 2.

**Fig. 2 Fig2:**
[figure not shown]
Schedule of enrolment, interventions, and assessments

#### Self-care activation

Self-care activation is measured, as achieving self-management is one of the most frequent consequences associated with patient empowerment [29]. In addition, there is evidence that patient activation is associated with health-related outcomes. It has been found that active people are more likely to have received preventive care, less likely to smoke or have a high BMI, and have better clinical indicators (systolic blood pressure, LDL). In addition, they are less likely to be hospitalised or use emergency services [40]. Self-care activation is measured using the Patient Activation Measure (PAM) instrument [41], which measures patient activation, a concept related to empowerment. The instrument covers the elements used to define empowerment (patients’ capacities, knowledge, behaviours and support by others) [42]. PAM measures individuals’ knowledge, skills and confidence to manage their own health. The questionnaire consists of 15 items on a 5-point Likert scale. Individuals fall into one of the following levels of activation along a 0–100-point scale: 1) Being overwhelmed and unprepared to play an active role in own health, 2) lacking knowledge and confidence for self-care, 3) taking action but lacking confidence and skill to support behaviours, 4) adopting health supporting behaviours, but may have difficulties to maintain them in stressing situations. The measure has proved to be highly valid and reliable with good psychometric properties, indicating its use in tailoring interventions and assessing changes. In this study, PAM scores are used to support patient activation individually. Creating situations where patients can experience success in taking control of their health is an essential part of effective self-care support [41, 43, 44].

#### Knowledge level

Knowledge is seen as essential for empowerment [29]. Knowledge tests have been used to measure the outcomes in educational interventions, to evaluate their effect or to monitor the learning progress during education [45]. Positive outcomes have been reported on disease-specific knowledge, adherence to medication and diet as well as on self-efficacy among people with chronic disease. A positive but inconsistent effect has also been reported in self-care and hospital readmission rates [37]. For this study, a knowledge test based on literature was developed in the research group consisting of a clinical nutritionist, a physician, nurses experienced on oncology and the researcher. A clinical nutritionist and two patient experts validated the test. The responses required (15 items) are either yes or no. Each correct answer gives one point and total score is the sum of correct answers. The knowledge test covers the following topics:
Malnutrition; definition and prevalence in patients with CRC (2 items)Impact of malnutrition on treatment, morbidity and mortality (2 items)Chemotherapy-induced side effects that may reduce nutritional status; reasons, manifestation and self-care (11 items)

#### Quality of life

QoL is measured as the risk of malnutrition is strongly associated with QoL in cancer patients initiating adjuvant chemotherapy [46]. Improved QoL is seen as a long-term consequence of patient empowerment [29]. QoL is assessed using the Functional Assessment of Cancer Therapy Scale – Colorectal (FACT-C) [47], which is a reliable and valid measure and sensitive to changes in functional status [48]. The questionnaire consists of 36 items on a 5-point Likert scale in four areas of wellbeing: physical (0–28 points), social (0–28 points), emotional (0–24 points), functional (0–28 points) and CRC subscale (0–28 points). Total sum is 0–136 points. Higher score means better QoL. Points are assigned for low level (0–34 points), satisfactory (34–68 points), average (68–102 points) and high level (102–136 points). FACT-C has been shown to have good overall validity and reliability, to be short, have flexible scoring, responsiveness to change in performance status, to be significantly correlated with other assessments of mood and show positive results in hypothesis testing [49, 50].

#### Risk of malnutrition

The risk of malnutrition is assessed as the educational intervention is presumed to prevent malnutrition or reduce the risk of malnutrition. In diagnostic assessment of malnutrition, the following criteria are recommended: non-volitional weight loss, low body mass index (BMI), reduced muscle mass, reduced food intake or assimilation and disease burden/inflammation [51]. To identify the patients at risk, we use the validated Nutritional Risk Screening 2002 tool (NRS2002) [52], which was developed to detect the presence of malnutrition and to predict whether malnutrition is likely to worsen due to patients’ illness [53]. Patients are assessed based on BMI, recent weight loss percentage and change in food intake (0–3 points), age (0–1 points) and severity of disease (0–3 points). The total sum is seven points. Patients with a total score of ≥3 are classified as nutritionally at risk.

#### Side effects

Side effect self-monitoring is used to assess the intensity of the side effects as well as to reinforce the intervention effect by reflecting on the self-care activities. After the first chemotherapy treatment, nurses give the self-monitoring diary to patients in both IG and CG, to be returned to the researcher after the fourth (or the last) chemotherapy cycle. Patients in IG document the side effects and their intensity as they appear (NRS 0–10; 0 = not at all, 10 = the worst possible) before and after the performed self-care activities. In addition, patients document their individual expectations for additional knowledge, and this information is used during the educational intervention. Patients in CG only self-monitor and document the intensity of each side effect as it appears (NRS 0–10; 0 = not at all, 10 = the worst possible).

#### Clinical data

Clinical data is gathered from electronic patients’ records. We are interested to find out whether the educational intervention is related to better adherence to treatment schedule. Therefore, data of patient-induced treatment changes, cancellations, transferring and interruptions are documented from baseline to 8 weeks. It has been indicated that worse nutritional status is related to greater morbidity [17]. Therefore, we collect data of patients’ emergency room visits and hospitalisation from baseline to 8 weeks.

The sample size was calculated to detect a 7-point mean difference in the PAM scale between groups assuming standard deviation of 11 points for both groups with 80% power and significance level of 0.05. This leads to required sample size of 40 participants per group. The meaningful difference between the average score of individuals who engage in healthy behaviours and those who do not is considered 4 points on the PAM scale [44]. To reach the target sample size (40 + 40), the researcher recruits participants by sending questionnaires with a research info and contacting them by phone the day before they visit the outpatient clinic. The researcher also meets the eligible participants to provide verbal information of the trial and answer questions. The strategies to improve patients’ adherence to the intervention protocol comprise the use of a self-monitoring diary and positive feedback from the research nurse. For individual participants, the intervention will be discontinued in the case of worsening condition, treatment change, or at their own request.

### Assignment of interventions

The researcher (LT) enrols the participants, and those willing to participate are randomly assigned to CG and IG using stratified randomisation according to stage of disease and existence of stoma. An allocation sequence using blockrand package [54] in R version 3.6.1 [55] was used. For each block, the block size was randomly chosen from a set of 2, 4 and 6. Allocation ratio of 1:1 was used. The statistician generated an unpredictable allocation sequence using sequentially numbered, opaque, sealed envelopes. The envelopes, numbered in advance, are opened sequentially after the participant’s name is written on the appropriate envelope [56]. The researcher (LT) allocates participants to the intervention with equal probability as a simple random sample is drawn from each group. Thus, the person enrolling participants does not know in advance which treatment the next person will get [39]. Patients' blinding is not possible as the RN informs the patients in IG of the one-hour educational session. The research nurse cannot be blinded because she provides the intervention. The data analyst is blinded as data are anonymised by using codes (001, 002 etc.).

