### Data collection

Baseline measurement (M0) is conducted before patients’ first contact in the outpatient clinic. Follow-up measurement (M1) is conducted 8 weeks after the intervention. The duration of a chemotherapy treatment varies from 3 to 6 months. The occurrence of chemotherapy side effects is individual and they are principally temporal being most severe in 3–7 days after each cycle. During the two-month follow-up period, patients have received four cycles of treatment, which is considered sufficient to assess the effects of the intervention. The researcher sends research information and baseline questionnaires (demographic data, PAM, knowledge test, FACT-C, NRS2002) to the patients with a return envelope enclosed. She contacts potential participants by phone before their first treatment to inform about the study and asks for their verbal consent. Patients return the questionnaires within a week before the first appointment in the outpatient clinic. In connection with this appointment, the researcher contacts the participants for verbal research info and written informed consent. Recruitment continues until the sample size is reached (40 + 40). The enrolment period will last 4–5 months based on calculated sample size and the assumption of 10 new CRC patients a week and that approximately 10% of the patients will refuse to participate. Outcome data is not collected on participants who suspend on their own initiative or deviate from intervention protocols. The researcher manages data confidentially by entering and storing data on a password-protected computer. Original study questionnaires are kept at the participating site. The researcher codes data for ease of data storage, review, tabulation, and analysis. Files in electronic and paper form will be discarded after the publication of the research results (2022). In the information letter, patients are instructed to report spontaneously any unintended effects to an outpatient clinic nurse. Nurses report these events to the physician and first author, who make the final decision to discontinue the study, if necessary. A formal data monitoring committee will not be set up due to the short duration of the study and the harms are known to be minimal.

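### One researcher both enrols and allocates and can know past allocations, so concealment is weakened; the reason given for it, a simple random sample, is not the method used

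*Protocol article*

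**What the plan says.** All of the following is in the protocol article, under Methods.

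- **Assignment of interventions, roles.** One researcher enrols participants. The same researcher "allocates participants to the intervention with equal probability as a simple random sample is drawn from each group".
- **Assignment of interventions, method.** Randomisation is stratified by disease stage and stoma, 1:1, in blocks: "the block size was randomly chosen from a set of 2, 4 and 6".
- **Assignment of interventions, safeguards.** A statistician generated the sequence. Envelopes are opaque, sealed and numbered in advance. The participant's name goes on the envelope before it is opened, and envelopes are used in order. The person who opens them is not named.
- **Assignment of interventions, conclusion.** "Thus, the person enrolling participants does not know in advance which treatment the next person will get". Patients and the intervention nurse are stated to be unblinded.
- **Intervention nurse.** "The researcher and research nurse will meet once a week to check that the protocol is adhered to".
- **Data collection.** The researcher posts the baseline (M0) questionnaires, phones patients for verbal consent and receives the M0 forms before the first appointment. Then: "In connection with this appointment, the researcher contacts the participants for verbal research info and written informed consent".

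**The concern.** The word Thus in the concealment sentence rests on a procedure that the trial does not use. Under simple randomisation an enroller who remembers every past assignment learns nothing about the next. Under small permuted blocks within strata, the arm that is behind is the more likely one to come next. The enroller here can know what has gone before in each stratum.

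There is also room to act on a guess. The same person phones patients, seeks consent in person after M0 has come back, and applies an exclusion for impairment preventing participation, which calls for judgement. If persuasion or timing shifted with the expected arm, the groups could differ in motivation for self-care. In an unblinded trial whose first primary outcome is a self-completed activation questionnaire, that difference would look like a treatment effect. Collecting M0 before allocation does not prevent this, because written consent is still sought after M0 is returned.

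**Working it through.** **1. The plan's own figure.** The sample-size paragraph (end of the Clinical data section) uses a difference of 7, SD 11, 80% power and alpha 0.05; the Data analysis section makes tests two-sided. The normal approximation gives n = 2 × (1.96 + 0.84)² × 11² / 7² ≈ 38.8, so 39 per arm. The t-test version gives 39.75, so 40. The stated 40 per group reproduces. SD 11 and 40 per arm are carried into step 4.

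**2. One case by hand.** Take a new stratum with one allocation made. The chance that the next goes to the other arm is 1 for a block of 2, 2/3 for a block of 4 and 3/5 for a block of 6. With the three sizes equally likely (an assumption), this is (1 + 2/3 + 3/5) / 3 = 0.756. A simple random sample would give 0.5.

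**3. Simulation.** Blocks were drawn at random from the stated sizes, with a separate envelope series per stratum. The number of stage levels is not given, so several stratum sizes were tried. The optimal guesser knows past allocations and the block-size set and updates exactly. The simple guesser does not know the sizes and picks the arm that is behind, or tosses a coin when level.

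| Patients per stratum | Optimal guess correct | Lagging-arm guess correct | Next arm certain |
|---|---|---|---|
| 7 | 66.9% | 66.7% | 3.0% |
| 13 | 68.5% | 68.3% | 3.5% |
| 20 | 69.7% | 69.5% | 3.8% |
| 40 | 70.0% | 69.9% | 3.9% |

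An enroller unaware of past allocations is right 50% of the time. Knowing the block sizes adds about 0.2 percentage points at most, so what matters is knowledge of past allocations.

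A count of highly predictable allocations depends on the cut-off. At 20 per stratum, 59% can be called with more than 75% confidence, 48% with more than 80%, 6.6% with more than 90%, and 3.8% with certainty. Block sizes of 4, 6 and 8 would lower the rate of correct guesses only to 64 to 68%.

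**4. What a guess could do.** Suppose enrolled patients differ by +ν or −ν points in expected PAM change according to the guessed arm, and the guess is right with probability p. Each arm's mean shifts by ν(2p − 1) in opposite directions, so bias = 2ν(2p − 1). With p = 0.69, 2p − 1 = 0.38. The standard error is 11 × √(2/40) = 2.46. Type I error is P(Z > 1.96 − bias/SE) + P(Z < −1.96 − bias/SE).

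| Assumed ν | Bias (points) | Bias/SE | Type I error |
|---|---|---|---|
| 0.5 | 0.38 | 0.15 | 5.3% |
| 1 | 0.76 | 0.31 | 6.1% |
| 2 | 1.52 | 0.62 | 9.5% |
| 3 | 2.28 | 0.93 | 15.3% |

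No value of ν comes from the documents. Because the main analysis compares change from M0 to M1, ν must be a difference in change; a stable difference in PAM level would largely cancel. SD 11 is the planning value and is assumed to apply to change.

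**The case against.** A reader might infer that this researcher opens the envelopes, was told the block sizes, and that concealment therefore fails. The documents do not support that reading. Envelope opening is described in the passive, and the researcher as opener is only a fair inference from the statement that the researcher allocates. No section says the researcher was given the block sizes. They are printed in an article that describes recruitment as ongoing, but step 3 shows that knowing them hardly matters.

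The safeguards are also genuine. Writing the name first guards against reassignment after opening, opaque sealed envelopes hide the content, and varying block sizes keep certainty rare: fixed blocks at 20 per stratum would make the next arm certain for 50% (size 2), 33% (size 4) or 22% (size 6). What remains is probabilistic guessing, present in any open blocked trial where past allocations are known. To produce the bias in step 4, the enroller would have to track each stratum and act on the guess throughout. The timing of envelope opening relative to written consent is not stated either.

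These points limit the size of the concern. They do not repair the sentence, which justifies concealment by a method that contradicts the one described beside it, and they do not separate enrolment from allocation.

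**Conclusion.** The point holds as a weakness in concealment and a contradiction in the text. One person enrols and allocates and can know earlier assignments, so that person's ignorance of the next arm is not guaranteed. The next arm could be guessed correctly 67 to 70% of the time instead of 50%, with certainty for about 3 to 4% of patients. This assumes equally likely block sizes, separate envelope series per stratum and 7 to 40 patients per stratum. The effect on type I error ranges from negligible (5.3%) to material (15.3%) over the assumed selection effects. Nothing in the documents shows that any selection has taken place. The change is worth making because it is cheap and the first primary outcome is self-reported in an unblinded trial.

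**What to change.** For the remaining patients:

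1. The enrolling researcher logs eligibility, written consent, stratum and receipt of M0.
2. Only then does someone who does not enrol open the next envelope of that stratum. The research nurse, already unblinded, is the natural choice. The statistician is suitable only if that person is not the blinded data analyst.
3. The researcher is not told individual allocations during recruitment, and the weekly adherence meetings use coded session logs.
4. Where feasible, the research nurse holds returned side-effect diaries unopened until recruitment closes. The Side effects section has both arms return them to the researcher, and their content differs by arm, so masking would otherwise be lost when they come back.
5. The simple random sample sentence is replaced by a description of stratified permuted blocks and this procedure.
6. The report states how patients already enrolled were allocated.

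Dropping block size 2 is optional and gains little.

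The cost is a short amendment, a slight delay before the arm is known, and some rerouting of logs and diaries. No extra staff or patients are needed. Masking of the researcher may still be incomplete.
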